## Abstract

**Background:**

Anxiety and depression are common co-morbidities in patients with chronic obstructive pulmonary disease (COPD). Serious implications can result from psychological difficulties in COPD including reduced survival, lower quality of life, and reduced physical and social functioning, increased use of health care resources and are associated with unhealthy behaviours such as smoking. Cognitive behavioural therapy (CBT) is a psychological intervention which is recommended for the treatment of many mental health problems including anxiety and depression. Unfortunately access to trained CBT therapists is limited. The aim of this study is to test the hypothesis that CBT delivered by respiratory nurses is effective in the COPD population. In this paper the design of the Newcastle Chronic Obstructive Pulmonary Disease Cognitive Behavioural Therapy Study (Newcastle COPD CBT Care Study) is described.

**Methods/Design:**

This is a prospective open randomised controlled trial comparing CBT with self-help leaflets. The primary outcome measure is the Hospital Anxiety & Depression Scale (HADS) – anxiety subscale. Secondary outcome measures include disease specific quality of life COPD Assessment Tool (CAT), generic quality of life (EQ5D) and HADS-depression subscale. Patients will be followed up at three, six and 12 months following randomisation.

**Discussion:**

This is the first randomised controlled trial to evaluate the use of cognitive behavioural therapy undertaken by respiratory nurses. Recruitment has commenced and should be complete by February 2014.

**Trial registration:**

Current Controlled Trials, ISRCTN55206395

## Background

COPD is an umbrella term used to describe chronic bronchitis and emphysema which cause irreversible obstruction of the airways. COPD is increasingly felt to be a systemic syndrome with multiple co morbidities. Anxiety and depression are amongst the most common co-morbidities in COPD. Cognitive behavioural therapy (CBT) is a psychological intervention which is recommended for the treatment of many mental health problems including anxiety and depression. A breathing test called spirometry measures how much air can be exhaled in 1 second (FEV_1_) and the forced vital capacity (how much air can be exhaled fully after a full inhalation). The severity of obstruction is defined as, mild (FEV_1_ > 80% predicted), moderate (FEV_1_ 50-79%), severe (FEV_1_ 30-49%) and very severe [1]. The main cause of COPD is smoking [2].

Symptoms of COPD are cough, sputum production, wheeze and breathlessness. Symptoms of COPD lead to a gradual progression of disability over many years. As a consequence day to day functioning is affected and quality of life is reduced [3,4]. Patients focus on feeling unwell, their inability to perform everyday activities, and on the emotional consequences of the disease [5]. People with COPD are two to three times more likely to experience mental health problems than the general population [6]. Serious implications for people with COPD and mental health problems include poorer clinical outcomes, lower quality of life, reduced ability to manage physical symptoms effectively and are associated with unhealthy behaviours such as smoking [6] and reduced survival [3].

A systematic review and meta-analysis reported the prevalence of clinically significant anxiety at 36% and 40% for depression in patients with COPD [7]. Anxiety is an unpleasant emotional state associated with fear and distressing physical symptoms including rapid breathing and shortness of breath [8]. These symptoms overlap with the symptoms of COPD [9]. Anxiety is a significant predictor of the frequency of hospital admissions and re-admissions for acute exacerbations of COPD [10].

Panic disorder is up to ten times more prevalent in patients with COPD than in the general population [11,12] Panic disorder consists of recurring, unforeseen panic attacks. This is followed by persistent worry about having further attacks. Panic attacks develop suddenly, are associated with intense fear, anxiety, and physical arousal and are relatively short lived [8]. In patients with COPD, worsening breathlessness is often interpreted in a catastrophic way. Patients commonly think they cannot breathe and death is imminent. Symptoms of increased physical arousal follow leading to an escalating cycle which results in panic [13]. Patients become anxious about becoming breathless and avoid exertion which may trigger unpleasant symptoms occurring. This leads to physical de-conditioning thereby compounding exertional breathlessness, reducing confidence, which collectively exacerbates the panic cycle.

Management of psychological problems in COPD remains poor [14]. Guidelines for the management of anxiety and depression [15,16] recommend psychological treatment, pharmacological treatment or both in combination. Psychological interventions include CBT, counselling and self-help approaches. There are a growing number of studies evaluating the efficacy of psychological interventions to improve the psychological well-being of patients with COPD. Most of the published studies have used cognitive behavioural therapy. There is some evidence in a systematic review that psychological interventions such as cognitive behavioural therapy impact on anxiety [14]. However, a meta-analysis revealed that most studies were under-powered and demonstrated a small effect for anxiety only [14]. There is a need for high-quality systematic research of CBT in the routine management of patients with COPD.

A brief cognitive behavioural treatment intervention has been developed specifically for patients with COPD. The Lung Manual Treatment Program is based on principles of CBT and self-management [17]. The intervention is undertaken by respiratory nurses and aims to reduce anxiety, depression, improve quality of life and have health economic benefits. A randomised controlled trial has been developed to evaluate the efficacy of a brief CBT intervention undertaken by respiratory nurses in this patient group. The design and methods of the study are now presented.

## Methods/Design

### Design

The Newcastle COPD CBT CARE study is a prospective two armed randomised controlled trial (RCT) with longitudinal follow up of 12 months. The main aim of the trial is to identify if respiratory nurse delivered CBT, reduces symptoms of anxiety in patients with COPD. Data will be collected three, six and 12 months following randomization. Data collected at each time point can be found in Table 1.

**Table 1 T1:** Outcome measures and time of assessment in Newcastle COPD CBT CARE study

	**Baseline**	**Follow up visit 1– 12–14 weeks**	**Follow up visit 2–6 months**	**Follow up visit 3–12 months**
Demographic Data	√	-	-	-
Gender	√	-	-	-
Age	√	-	-	-
Smoking Status & pack years	√	-	-	√
Ethnic Group	√	-	-	-
Marital Status	√	-	-	√
Education	√	-	-	-
Inhaler Technique	√	-	-	-
HAD - A	√	√	√	√
HAD - D	√	√	√	√
CAT	√	√	√	√
EQ5D	√	√	√	√
Spirometry	√	-	-	-
Oxygen saturations	√	-	-	-
MRC Dyspnoea Score	√	-	-	-
Co-morbidities	√	√	√	√
BMI	√	√	√	√
Medication	√	√	√	√
Health care utilisation (primary & secondary care)	√	-	-	√
Participation in pulmonary rehabilitation	√	√	√	√

√ refers to data collected at each visit.

### Primary outcome

The primary objective is to investigate if CBT delivered by respiratory nurses with either advanced CBT training (Post Graduate Diploma) or basic training in CBT techniques, reduces anxiety. The HADS Hospital Anxiety & Depression Scale (HADS) will be used to measure anxiety. Patients will be followed up at three, six and twelve months following randomisation into the study. The effects of the CBT intervention will be compared to usual care. A standardised manualised brief CBT intervention will be used. 224 patients will be required to complete the primary outcome at three months (112 in each arm). Patients will be stratified according to severity of COPD and age at randomisation.

### Secondary outcomes

Six questions have been developed as secondary outcomes. Firstly, does CBT delivered by respiratory nurses reduce hospital admissions in the 12 months following randomisation? Secondly, does CBT delivered by respiratory nurses reduce anxiety at six and 12 months compared to standard care? Thirdly, identify if CBT more effectively delivered by basic (three day short course) CBT trained respiratory nurses or advanced (postgraduate diploma in CBT) CBT trained respiratory nurses? Fourth, if CBT delivered by respiratory nurses reduce depression as measured by Hospital Anxiety and Depression Scale – Depression (HADS-D) at three, six and 12 months compared to standard care? Fifth, does CBT delivered by respiratory nurses improve patient quality of life at three, six & 12 months as measured by a reduction in COPD Assessment Tool (CAT) and EuroQol 5 Dimension questionnaire (EQ5D) scores? Finally, can this study inform design of a multicentre RCT?

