### Randomisation

Patients enrolled in the study are randomised on a 1:1: basis to CBT or control using a computer generated software package after signing the consent form. Patients are stratified at randomisation for COPD disease severity using NICE 2010 categories (mild to moderate and severe to very severe) and age. Patient initials, date of birth and severity of COPD are entered into the web-based system, which returns the allocation status. Patients are informed of their treatment group following randomisation.

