### CBT intervention

The study intervention involves standard care plus a brief CBT based program delivered by respiratory nurses. Clear manualised treatment will be used to ensure the CBT based treatment can be replicated. A manualised protocol has been specifically developed for this study by the Respiratory Nurse (KH) & Consultant Psychologist (CB). The CBT will be delivered by four respiratory nurses (two trained to Post Graduate Diploma Level and two who have completed a three day training course at foundation level). Monthly clinical supervision will be provided for all four nurses by a Consultant Clinical Psychologist (CB). The intervention will be delivered to individual patients in either in a respiratory clinic in secondary care or within the patients’ home. The CBT intervention is tailored to the patient’s individual needs (within the boundaries of the manual). Patients will be offered between two – six sessions of therapy as required. The number of sessions will be based on the patient’s progress and HADS scores. The first session will take 30–60 minutes. Subsequent follow up sessions will take up to 30 minutes.

The intervention includes the following processes. The nurse assesses the patient’s reported current difficulties and develops an individualised treatment plan. The treatment plan may include the development of coping strategies including goal-setting, identifying, challenging and changing negative thoughts, distraction, breathing control, problem-solving, activity scheduling/diary, relaxation, weighing up pros and cons; positive logs, learning to respond appropriately to symptoms and reducing avoidance and safety behaviours that maintain anxiety and low mood.

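### The basic-versus-advanced training question rests on two nurses per level, so training cannot be reliably separated from the individual nurse, and the question should be restated as descriptive

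*Protocol article*

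**What the plan says.** The Secondary outcomes section lists six questions. The third is to "identify if CBT more effectively delivered by basic (three day short course) CBT trained respiratory nurses", with diploma-level nurses as the comparator. It asks which level works better, and it is not labelled exploratory.

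The CBT intervention section fixes the therapists at four: "two trained to Post Graduate Diploma Level and two who have completed a three day training course at foundation level".

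The Design section describes two arms. Under Randomisation, "Patients enrolled in the study are randomised on a 1:1: basis to CBT or control using a computer generated software package". On strata, the section says: "Patients are stratified at randomisation for COPD disease severity using NICE 2010 categories (mild to moderate and severe to very severe) and age". On the mechanics, it says: "Patient initials, date of birth and severity of COPD are entered into the web-based system, which returns the allocation status". Neither nurse nor training level appears in this scheme, and no section says how a patient in the CBT arm reaches a particular nurse.

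The Sample size section covers CBT versus control only. The Analysis section names a *t*-test for HADS-A at three months and a longitudinal model with assessments nested in patients. It describes no analysis for the training question.

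**The concern.** To say which training level delivers CBT more effectively, one must attribute a difference between groups of patients to training. With two nurses per level, the contrast also carries whatever else distinguishes those two pairs of people, such as skill, experience or rapport. More patients per nurse give a more precise picture of those four nurses. They do not give more nurses per level.

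Caseload is a second, conditional problem. Allocation as described stops at the arm, so if nurses are not assigned at random, the patients seen at each level may differ. Delivery in clinic or at home is one way this could happen.

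The answer could be used. The Discussion presents the study as addressing the teaching of CBT skills to staff outside mental health, against a shortage of therapists. The sixth secondary question is whether the study can inform a multicentre trial. A difference could reflect one able nurse, and a null result could be taken to mean that three days of training match a diploma. The design supports neither conclusion.

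**Working it through.** **Inputs from the Sample size section:** 112 completers per arm, difference 1.5 HADS-A points, SD 4, type I error 5%, power 80%.

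**Input from the CBT intervention section:** two nurses per level.

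**Assumptions:** two-sided testing; an even split of the CBT arm (112/2 = 56 patients per level, 56/2 = 28 per nurse); nurse ICC from 0 to 0.10, since the article gives none.

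**Step 1. The plan's own figure.** n per arm = 2 × (1.96 + 0.84)² × 4² / 1.5² = 112 after rounding up. Power at 112 per arm is 80.1% (79.8% with the noncentral *t*). The stated figure reproduces.

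**Step 2. Training comparison, nurse ignored.** SE = 4 × √(2/56) = 0.756. Power for 1.5 points is 50% (noncentral *t*; 51% by the normal approximation). The difference detectable with 80% power is (1.96 + 0.84) × 0.756 = 2.1 points, or 0.53 SD, against the trial's main target of 1.5 points.

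**Step 3. Nurse as the unit.** A nurse mean has variance 16 × [ICC + (1 − ICC)/28]. The difference between two averages of two nurses has that same variance, because 1/2 + 1/2 = 1. Degrees of freedom are 4 nurses − 2 levels = 2, with critical *t* = 4.30.

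For example, at ICC 0.02: 16 × (0.02 + 0.98/28) = 0.88, so SE = 0.938 and the 95% half-width is 4.30 × 0.938 = 4.0 points.

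**Step 4. If a patient-level test were used.** Its nominal SE stays at 0.756, so its true type I error is 2 × [1 − Φ(1.96 × 0.756 / SE)].

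| Assumed ICC | SE | 95% half-width, 2 df | Power for 1.5 points, 2 df | Difference for 80% power | Type I error of a patient-level test |
|---|---|---|---|---|---|
| 0 | 0.756 | 3.3 | 22% | 4.3 | 5% |
| 0.01 | 0.852 | 3.7 | 18% | 4.8 | 8% |
| 0.02 | 0.938 | 4.0 | 16% | 5.3 | 11% |
| 0.05 | 1.159 | 5.0 | 12% | 6.6 | 20% |
| 0.10 | 1.454 | 6.3 | 9% | 8.2 | 31% |

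**Step 5. Limit with unlimited patients.** As patients per nurse grow, the SE tends to 4 × √ICC, which is 0.9 points at ICC 0.05, and the degrees of freedom stay at 2.

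**The case against.** The best case for the plan has five parts.

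- **The article is a condensed account.** How patients reach nurses is operational detail that a full protocol may give. This stands. A reader might infer that diploma-level nurses were sent the harder cases, but no section says so. Caseload imbalance is a possibility, not a documented fact. Random assignment to nurses would remove it and still leave two nurses per level.
- **No test is specified for this question.** This also stands. A reader might infer that a patient-level test with inflated error is planned. The Analysis section ties its *t*-test to the primary outcome, so the 11% to 20% applies only if such a test were used. Nor does the article claim equivalence between levels.
- **Secondary questions need not be powered.** True, and low power alone would not be a finding. Here the attribution to training is unreliable whatever the number of patients, and an analysis plan cannot add nurses.
- **The plan limits variation between nurses.** All four share a manual and monthly supervision, data are collected on consistency across nurses, and 60 sessions are video recorded for independent assessment. This may lower the nurse ICC. It does not remove the confounding, and even at ICC 0 the nurse-level test has only 22% power.
- **A nested analysis is possible.** It is, on 2 degrees of freedom. The accurate statement is that training and nurse cannot be separated reliably.

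**Conclusion.** The point holds for the third secondary question. As worded, it asks for a comparison of training levels that two nurses per level cannot reliably support. That part rests on counts stated in the article. The caseload part is conditional on how patients are assigned to nurses, which is not stated.

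The size of the problem depends on the assumed even split and ICCs, but the conclusion does not turn on the ICC: nurse-level power for 1.5 points runs from 22% at ICC 0 to 9% at ICC 0.10.

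A reader might carry this over to the main result. The documents do not support that: the primary objective pools both training levels, the comparison of CBT with control is randomised, and its sample size reproduces.

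**What to change.** Restate the third secondary question as exploratory and descriptive. Report baseline-adjusted HADS-A results and session counts by nurse and by training level. Any interval for a training level, or for the difference between levels, should treat the nurse as the unit. State that no superiority or equivalence claim will be made between training levels. It would also help to say how patients in the CBT arm are assigned to nurses.

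The cost is the comparative claim and nothing else. Baseline HADS-A is already collected, and the mean number of sessions is already a process measure.

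Changing the assignment of patients still to be recruited is not recommended. Recruitment has commenced, so a change would mix two assignment schemes, and each level would still have two nurses.

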### Setting

The setting for this study is an urban population in the North East of England. Patients who attend the respiratory clinics at Newcastle upon Tyne Hospitals NHS Foundation Trust with a diagnosis of COPD are routinely asked to complete a HADS questionnaire. All patients with a confirmed diagnosis of COPD with an FEV1/FVC ratio <0.7 who have a HADS score of ≥8 are offered information about the study. The unit already runs a respiratory nurse led CBT service, supervised and supported by a Consultant Clinical Psychologist (CB). Patients are offered between two and six individualised CBT appointments.

### Research governance

Approvals for this study were obtained from Sunderland Regional Ethics Committee. The trial has been entered onto the U.K. NIHR Clinical Research Network (CRN) Portfolio (Reference UKCRN Study ID: 10519; http://public.ukcrn.org.uk/search/StudyDetail.aspx?StudyID=10519 and ISRCTN study 55206395).

### Inclusion criteria

• Patient with a confirmed diagnosis of COPD (FEV1/FVC ratio <70% [5].

• All levels of COPD disease severity will be eligible including mild to moderate (FEV1 >50% predicted) and severe to very severe (FEV1 <50% predicted).

• Patients with HADS –anxiety subscale scores of ≥8.

• Willing to participate in the study and provide written consent.

• Agree to attend a minimum of two and maximum of six CBT sessions.

### Exclusion criteria

• Patients with a HADS-A score <8.

• Patients with known psychiatric history such as psychosis.

• Patients currently receiving psychological talking therapy including CBT treatment.

• Patients with cognitive impairment (e.g. dementia).

• Patients involved in any other interventional clinical trial.

### Randomisation

Patients enrolled in the study are randomised on a 1:1: basis to CBT or control using a computer generated software package after signing the consent form. Patients are stratified at randomisation for COPD disease severity using NICE 2010 categories (mild to moderate and severe to very severe) and age. Patient initials, date of birth and severity of COPD are entered into the web-based system, which returns the allocation status. Patients are informed of their treatment group following randomisation.

### Standard care

Both groups receive standard medical care which involves recording spirometry, oxygen saturation levels and HADS questionnaire at each routine medical clinic visit. Patients randomised to standard care arm of this study are provided with written information on anxiety and/or depression (Northumberland, Tyne & Wear Mental Health Trust leaflets). Patients are advised to contact their primary care team should further help be required. Treatment in primary care will be directed by primary care team and is not part of the trial intervention. It may include psychotherapy, counselling, antidepressants and/or anxiolytics. Information on primary care directed interventions will be recorded at each study follow up visit.

### CBT intervention

The study intervention involves standard care plus a brief CBT based program delivered by respiratory nurses. Clear manualised treatment will be used to ensure the CBT based treatment can be replicated. A manualised protocol has been specifically developed for this study by the Respiratory Nurse (KH) & Consultant Psychologist (CB). The CBT will be delivered by four respiratory nurses (two trained to Post Graduate Diploma Level and two who have completed a three day training course at foundation level). Monthly clinical supervision will be provided for all four nurses by a Consultant Clinical Psychologist (CB). The intervention will be delivered to individual patients in either in a respiratory clinic in secondary care or within the patients’ home. The CBT intervention is tailored to the patient’s individual needs (within the boundaries of the manual). Patients will be offered between two – six sessions of therapy as required. The number of sessions will be based on the patient’s progress and HADS scores. The first session will take 30–60 minutes. Subsequent follow up sessions will take up to 30 minutes.

The intervention includes the following processes. The nurse assesses the patient’s reported current difficulties and develops an individualised treatment plan. The treatment plan may include the development of coping strategies including goal-setting, identifying, challenging and changing negative thoughts, distraction, breathing control, problem-solving, activity scheduling/diary, relaxation, weighing up pros and cons; positive logs, learning to respond appropriately to symptoms and reducing avoidance and safety behaviours that maintain anxiety and low mood.

### Quality control of manualised CBT program

Quality control will be maintained through adherence to the study protocol, the principles of good clinical practice, research governance and clinical trial regulations. Data is being collected to assess consistency of intervention delivered in the treatment arm across nurses and principles of delivery of CBT. Sixty (5%) of the CBT sessions will be video recorded to validate adherence to the CBT manual and the quality of the CBT intervention. The assessment is undertaken by a CBT therapist independent of the study delivery team with feedback given as needed.

